**Figure 1 figure1:**
[figure not shown]
Visualization of the age-cohort design to compare students of the same age within the same schools over time, in relation to the Sustainable Innovation for Children Transporting Actively Intervention. T0 denotes baseline (2024), and T1 denotes follow-up (2025).

### Study Sample

In collaboration with the municipality involved in the project, public schools involving grades 4 to 6 will be identified, and invitations will be sent to principals to participate. Upon acceptance of participation by school principals, all children in grades 4 to 6, along with their parents and teachers at the participating schools, will be invited to participate in the study.

### Data Collection and Measurements

For all the research questions, data will be collected from the children and their parents at 2 time points, baseline (T_0_) and follow-up (T_1_). In addition, data will be collected from teachers at follow-up (T_1_). Multimedia Appendix 1 provides an overview of the data collection, including instruments used at baseline and follow-up. A detailed description of data collection and analysis is provided in the following sections for each research question. The baseline data collection is planned to be performed during 2 weeks in late fall 2024, and the data collection following the intervention is planned to be performed exactly 1 year later, 2 weeks after the 4-week SICTA intervention has ended, in line with the age-cohort design (Figure 1).

### Research Question 1

The number of weekly active school transports (0-10) will be collected using the wASTapp [36]. The wASTapp is a web-based form developed to enable daily self-reports of transportation mode, time, and distance and has shown satisfactory criterion validity when tested in children in grades 4 to 6. In the wASTapp web-based form, children are able to report their daily transport either in the classroom guided by their teachers (using school computers) or on their own phones. Children who report via their phone will receive a daily SMS text message containing a link to the web-based form. If children lack access to a school computer or mobile phone for completing self-reported questions, paper-based reporting will be provided as needed.

### Research Question 2

Data on CIM will be collected using the CIM License questionnaire [37]. The questionnaire consists of 6 questions with “yes” and “no” answer options and assesses the level of independent mobility in children.

### Research Question 3

To assess psychosocial aspects in children and parents, 2 questionnaires will be used: PILCAST (parents’ intention to let their child use active school transportation) [38] for parents and BRACS (behavioral regulation in active commuting to and from school)-Sweden [39] for children. PILCAST, based on the theory of planned behavior, includes 32 items on parents’ intentions, attitudes, norms, and perceived control and is assessed with 7-point Likert scales [38]. It also covers the transtheoretical model and sociodemographic characteristics such as gender, academic year, distance to school, and parents’ education level. BRACS-Sweden is based on self-determination theory and assesses children’s motivation to use AST using 23 items measuring intrinsic motivation, various types of regulation, and amotivation on a 5-point Likert scale [39]. It also includes sociodemographic details such as gender, distance to school, and academic year.

### Research Question 4

Sustainable health care aims to maintain or restore health while minimizing environmental harm and ensuring future generations’ health. The sustainable value equation [40], developed in health care research, will be used to analyze outcomes for patients and populations, considering financial, environmental, and social impacts [41].

To evaluate the sustainability of the intervention, we will use data collected at baseline and following the intervention, applying the triple bottom line equation. Data on intervention outcomes are changes in AST, which will be retrieved from child reports in wASTapp and evaluated in relation to the environmental, social, and financial impacts of the intervention, as described in detail in the following sections.

### Data Collection on Environmental Impact

The environmental impact will be calculated on the basis of AST reports (wASTapp), where calculations will be conducted to evaluate changes in motorized transport, and the corresponding carbon dioxide emissions will be retrieved from standardized models provided by the Swedish Meteorological and Hydrological Institute [42].

### Data Collection on Social Impact

Social impact will be estimated using data obtained from self-reported questions on psychosocial aspects among the children (BRACS and CIM License) and parents (PILCAST) [37-39]. We will also collect data on social impact from teachers participating in the project using a questionnaire on aspects of the feasibility of the intervention, in accordance with the study by Bowen et al [43]. The questionnaire covers 5 domains: demand, acceptability, implementation, practicality, and limited efficacy. Demand represents documented use, while acceptability encompasses suitability, attractiveness, and reactions to the procedure. Implementation reflects the degree of execution, including aspects such as fidelity (the extent to which the intervention is delivered as intended) and dose (the amount of the intervention delivered or received). Practicality considers positive or negative effects and the feasibility of carrying out the procedure. Finally, limited efficacy indicates the intervention’s potential for success [43].

### Data Collection on Financial Impacts

The intervention costs are limited to the cost of the teachers for the time they devote to the intervention. Teachers delivering the intervention will be instructed to keep a record of time devoted to preparing, delivering, and following up on the intervention.

### Data Analysis

#### Quantitative Analysis

For all research questions, descriptive statistics will be used to summarize the data. Categorical variables will be reported as frequencies and percentages, and continuous variables will be reported as means and SDs or medians and IQRs, depending on distributional characteristics. Before the main analyses for research questions 1 to 3, the design effect will be evaluated to account for clustering within schools. Specifically, the intraclass correlation coefficient will be estimated for each outcome using an unconditional linear mixed-effects model with school as a random intercept [44]. For research questions 1 to 2, the data (wASTapp and CIM) are planned to be treated as continuous outcomes, as the wASTapp measure is based on a 0 to 10 scale and the CIM variable will be operationalized as an index ranging from 0 to 6, derived from 6 items. Changes from baseline (T_0_) to follow-up (T_1_) will be analyzed using an analysis of covariance, with T_1_ as the dependent variable and T_0_ included as a covariate. The models are planned to be adjusted for sociodemographic characteristics. For research question 3, associations between psychosocial factors, sociodemographic characteristics, and AST will be analyzed using analysis of covariance, with AST at follow-up (T_1_) as the dependent variable and baseline values (T_0_) included as a covariate. For all research questions (1-3), model assumptions will be assessed, and the final choice of regression model will be guided by the distribution of the outcomes. Although the outcomes are planned to be treated as continuous, alternative approaches (eg, ordinal models) will be considered if this is not supported by the data [45]. If clustering within schools is present, corresponding mixed-effects models will be applied. Missing data will be examined for extent and patterns [45]. If missing at random is considered plausible, multiple imputation will be used. Sensitivity analyses will include complete case analyses to assess robustness. A significance level of .05 will be applied. All analyses are planned to be conducted using SPSS (version 31; IBM Corp).

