
### Sustainable Innovation for Children Transporting Actively: Development of the Intervention

The research project Sustainable Innovation for Children Transporting Actively (SICTA) was formed as a 4-week school-based intervention initially developed in 2016 in Sweden [25]. The SICTA intervention is based on theory, with 3 main concepts: social cognitive theory, empowerment, and gamification. Social cognitive theory involves factors related to AST behavior, including knowledge, self-efficacy, outcome expectations, short- and long-term goals, facilitators, and impediments to change. Moreover, empowerment facilitates the involvement of end users—children, teachers, and parents—in outlining the intervention. Gamification, which is the use of game design in a nongame context, is used to motivate children to participate in the intervention and perform assignments that are applicable to their route to school. The assignments are integrated into the curriculum; for example, one assignment could involve counting people and animals encountered during AST and analyzing these data in math classes. A long-term goal is also to track the number of kilometers walked and cycled by the class during the project. Thus, in line with the idea of gamification, when completing assignments, children receive rewards when they are accomplished. The intervention consists of 5 different steps: engaging parents through a parental meeting, increasing children’s knowledge of active transport, preparing weekly assignments for the children, encouraging walking and cycling to school over 4 weeks, and finally celebrating their achievements. At the parental meeting, parents are provided with information about the intervention, its benefits for AST, and an opportunity to discuss any concerns or perceived risks. To support teachers, they have access to an online platform called the Teacher’s portal. The assignments developed in the portal use innovative, game-based, student-centered pedagogical approaches that are integrated into contemporary school curricula. The criteria used during the development process included ensuring that the activities had a scientific foundation in educational research, an explicit connection to syllabi, opportunities for student influence, and the incorporation of peer collaboration. Therefore, it is evident from the previous description that the SICTA intervention is complex, involving multiple components and requiring skills from both the deliverers and the recipients [26]. Its complexity also arises from the flexibility of the intervention’s components and delivery, as well as the dynamic interactions between the intervention, its context, parents, children, and teachers. This adaptability ensures alignment with each school’s unique structure and functionality. In addition, guidelines stress the importance of considering both the intervention’s components and their interactions with the environment [26].

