The SICTA intervention has been designed and piloted with a focus on feasibility and practical implementation within school contexts, as demonstrated in several research studies [27-32]. Building on social cognitive theory and incorporating the concepts of empowerment and gamification [25] has proven to be a solid foundation for success in previous research. Reviews on promoting AST in school settings emphasize the importance of using theoretical frameworks [24,48,49]. Our study also introduces a research-based, user-friendly digital teacher portal for promoting AST within the school context, which may contribute to the maintenance and sustainability of the intervention. To balance the need for rigorous research with the practical constraints of real-world school settings, some pragmatic adaptations will be made. These adaptations address mainly the implementation, considering the limited time and resources available in schools. On the basis of the key concept of empowerment and findings from a pilot study [32], it was evident that teachers prefer flexibility in the intervention’s layout. Therefore, they will have the freedom to choose the content and the number of assignments for students during the project period.

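### Clustering is modelled only if an undefined school-level check finds it, and only at school level, although the contrast is year within school and delivery is by class; standard errors may therefore be wrong, and too small if outcomes vary by class or school-year

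*Protocol article*

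**What the plan says.** Under Quantitative Analysis, the article says that before the main analyses for research questions 1 to 3 "the design effect will be evaluated to account for clustering within schools". To that end, "the intraclass correlation coefficient will be estimated for each outcome using an unconditional linear mixed-effects model with school as a random intercept". The main model for research questions 1 and 2 is an analysis of covariance "with T_1_ as the dependent variable and T_0_ included as a covariate"; research question 3 has the same form, with AST at follow-up as the outcome. Clustering enters only afterwards: "If clustering within schools is present, corresponding mixed-effects models will be applied". The test level is fixed: "A significance level of .05 will be applied". The section does not say what size of ICC, or what test, counts as clustering being present, and it names no class, teacher or school-by-year level.

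Other sections describe how the data arise. Study Design sets the comparison as same-age pupils in the same school, 2024 against 2025. Study Sample invites all of grades 4 to 6. The Abstract names teachers as the deliverers. The section on the development of the intervention gives a shared class goal, to "track the number of kilometers walked and cycled by the class during the project". Research Question 1 allows pupils to report in the classroom under teacher guidance. Expected Contributions says of the teachers that "they will have the freedom to choose the content and the number of assignments for students during the project period".

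**The concern.** The plan's one clustering quantity is the school ICC. In a comparison of two years within the same schools, whatever is stable about a school is in both years and largely drops out of the difference. What remains is variation that differs between the two years in a school (school-by-year) and between classes. The article's own account of delivery gives reasons to expect both: content and number of assignments differ by teacher, the kilometre goal is shared by a class, and reporting may be done class by class. A school ICC from a school-only model does not isolate these sources, and a school random intercept does not put them into the standard error of the year effect.

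At stake is the error rate of the test on research question 1, the main effectiveness question, in a study without a concurrent control group. The decision to model clustering would also rest on an undefined look at the data.

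**Working it through.** **Inputs from the article.** Alpha 0.05 (sidedness not stated; two-sided assumed); grades 4 to 6 at both waves; contrast of year within school. There is no sample size, ICC or power figure to reproduce.

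**Assumed inputs.** J = 10 schools; 3 grades × 2 classes = 6 classes per school per year; 15 children per class, so n = 90 per school per year; total variance 1. Variance shares: school s, school-by-year sy, class c, persistent child p, residual e = 1 − s − sy − c − p.

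**Formulas, for pooled T0 and T1 records with a year term.** The school effect cancels in the T1 minus T0 difference of a school's means, leaving

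true variance per school = 2·sy + f·2c/6 + f·2p/n + 2e/n.

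Here f = 1 if no class or child is shared between waves. If grades 4-5 at T0 are the same classes and children as grades 5-6 at T1, only the leaving grade 6 and the entering grade 4 fail to cancel, so f = 1/3.

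A model with only a school intercept uses 2(1 − s − sy/2)/n. An analysis ignoring clustering uses 2/n. With R = true SE / model SE, real type I error = 2[1 − Φ(1.96/R)].

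**Worked case** (s = 0.05, c = 0.05, sy = 0, p = 0, no overlap): true = 2(0.05)/6 + 2(0.90)/90 = 0.0367; model = 2(0.95)/90 = 0.0211; R = √1.737 = 1.32; type I error 13.7%.

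**Results, school intercept only** (s = 0.05, except 0.10 in the two rows with c = 0.10):

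| Overlap | c | sy | p | R | Type I error |
|---|---|---|---|---|---|
| No | 0 | 0 | 0 | 1.00 | 5.0% |
| No | 0.02 | 0 | 0 | 1.14 | 8.5% |
| No | 0.05 | 0 | 0 | 1.32 | 13.7% |
| No | 0 | 0.01 | 0 | 1.40 | 16.0% |
| No | 0.05 | 0.01 | 0 | 1.64 | 23.2% |
| No | 0.10 | 0.02 | 0 | 2.14 | 36.0% |
| Yes | 0 | 0 | 0.5 | 0.81 | 1.5% |
| Yes | 0.05 | 0 | 0.5 | 0.93 | 3.5% |
| Yes | 0.05 | 0 | 0 | 1.10 | 7.5% |
| Yes | 0.05 | 0.01 | 0.5 | 1.34 | 14.5% |
| Yes | 0.10 | 0.02 | 0.5 | 1.76 | 26.5% |

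**Dropping the school intercept.** With school variance alone (s = 0.05), ignoring school gives R = √0.95 = 0.97 and type I error 4.4%, slightly conservative.

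**Larger classes.** With m = 20 children per class, C = 6 classes and no overlap, take shares of the variance left after the school effect. The inflation is 1 + (m − 1)c + (Cm − 1)sy:
- c = 0.05, sy = 0: 1 + 0.95 = 1.95, type I error 16%.
- c = 0.05, sy = 0.01: 1 + 0.95 + 1.19 = 3.14, 27%.
- c = 0.10, sy = 0.02: 1 + 1.90 + 2.38 = 5.28, 39%.

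**Simulation.** With 15 per class and 2,000 runs per scenario, the school-intercept model rejected in 12.2% (c = 0.05) and 25.9% (c = 0.05, sy = 0.01) without overlap. With overlap and p = 0.5 it rejected in 1.3%, 3.6%, 15.4% and 28.1% for the four matching rows. A paired t test on school-level differences held 3.8-6.1% in all seven scenarios. With 20 per class and 1,000 runs, the school-intercept model gave 14.3%, 30.7% and 41.5%, and the analysis without clustering 13.1%, 28.9% and 39.8%.

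**The case against.** The strongest reply has five parts.

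1. A reader might infer that the conditional rule itself makes the year test anti-conservative. It does not: leaving out the school intercept alone is slightly conservative, and in the simulations with 20 per class the analysis without clustering rejected a little less often than the one with a school intercept. The rule is at fault because it is undefined and looks at the wrong level for this contrast. It could shrink standard errors for between-school covariate associations in research question 3.

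2. A reader might infer that standard errors will be too small, and false positives several times too frequent. The documents do not support that certainty. Grades 4-5 at T0 are eligible again as grades 5-6 at T1; ignoring that correlation widens the model's standard error, and with no school-by-year variance the test can be conservative. This stands, and fixes the wording at may.

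3. The written model regresses T1 on T0 and has no year term. This also stands: the figures apply to the Study Design contrast fitted to pooled records. In a model of T1 outcomes only, a school intercept absorbs school-by-year variation, and the two cannot be separated.

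4. A reader might infer that the ICC check has little power. The number of schools is not given and no significance test is stated. If an F test were used, power would be near certain with 10 schools of 240 children at ICC 0.05, but about 23% with 6 schools of 60 at ICC 0.01. The point does not depend on this.

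5. A condensed article may leave further levels and degrees of freedom to a fuller plan. That is fair for degrees of freedom. But this article states a rule, conditional and school-only, and following it leaves class and school-by-year variance out.

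**Conclusion.** The point holds in this limited form. The stated rule conditions on an undefined school-level check and models school only, while the contrast and the delivery point to school-by-year and class. Under the assumed values, real type I error is about 8-40% when classes or school-years vary and no children are shared between waves. With full overlap and a persistent child share of 0.5, it runs from about 1.5% to about 15% at school-by-year 0.01, and higher in the heaviest setting tabulated. The direction is therefore not certain; what is certain is that the planned standard error ignores the components that determine it.

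Every variance share, and the numbers of schools, classes and children, is an assumption. Full overlap is an extreme, since it needs the same children to take part twice in intact classes. Class variation produced by how teachers deliver the programme arises only at T1 and so would not cancel even then. The caution in Expected Contributions against causal reading does not correct a standard error.

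**What to change.** Delete the conditional sentence and account for clustering by design, whatever the ICC turns out to be.

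- **Year contrast, research questions 1 and 2:** analyse pooled T0 and T1 records with a year term, with effects for school, school-by-year and class, and for child where records can be linked across waves. Use Kenward-Roger or Satterthwaite degrees of freedom. Report a paired school-level T1 minus T0 analysis as a check.
- **Models of T1 outcomes only, such as research question 3 as written:** include school and class. Do not add a school-by-year term, which cannot be separated from school there.
- **ICCs:** report them descriptively only.

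The cost is analysis wording and a class identifier on each record. The article describes follow-up collection as still ongoing, so the identifier may still be obtainable. Confidence intervals will often be wider.

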## Methods

### Study Design

An age-cohort design will be applied to evaluate the effectiveness of the SICTA intervention on children’s AST [35]. In an age-cohort design, same-age students within the same schools are compared over time (Figure 1). For example, students in fifth grade at baseline (T_0_) will be compared with students in fifth grade from the same school at follow-up (T_1_) 1 year later. With such a study design, possible age-related maturational differences between the comparison groups are controlled. The SICTA intervention is evaluated using this age-cohort design, where students at baseline (late fall 2024) will be compared with same-aged students from the same schools 1 year later at follow-up (late fall 2025) after receiving the intervention (implemented in late fall 2025). The study was registered in the Swedish national research database Researchweb (project 283668) on October 25, 2024.

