Our previous results highlight the complexity and challenges of conducting controlled research among school children [33]. Given these challenges, we have chosen an age-cohort design [35] to evaluate the SICTA intervention. This approach is particularly well suited for studying school-based interventions, as it allows for the examination of developmental changes over time while maintaining the feasibility needed for real-world implementation [46,47]. Age-cohort designs offer several advantages in this context. By following different age groups as they progress through school, this method enables a longitudinal perspective on intervention effects without requiring random assignment [35,47]. This not only improves practical feasibility but also minimizes issues such as ethical concerns, interference, and contamination—challenges often encountered in school-based studies [47]. In a previous pilot RCT of the SICTA intervention, significant participant attrition due to study design constraints further underscored the need for a more adaptable approach [33]. Additionally, age-cohort designs align well with the practice-based evidence framework, which is increasingly emphasized in public health research [46]. Many school-based interventions are implemented as natural experiments, making it essential to adopt methodologies that reflect real-world conditions rather than rigid experimental controls. By using an age-cohort design, we can capture broader trends within the school context while enhancing the generalizability of our findings [47]. However, given the pragmatic age-cohort design and real-world implementation, the findings should be interpreted as reflecting changes associated with the intervention rather than causal effects. In line with the Medical Research Council framework for complex interventions, effectiveness in this study refers to the extent to which the intervention may produce intended outcomes under real-world conditions, acknowledging contextual variability and implementation flexibility [26].

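### Imputation hangs on an untestable missing-at-random judgement, and the one named robustness check cannot detect departures from that assumption

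*Protocol article*

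**What the plan says.** The rule for missing data is in the protocol article under Data Analysis, Quantitative Analysis. First, "Missing data will be examined for extent and patterns". Then: "If missing at random is considered plausible, multiple imputation will be used. Sensitivity analyses will include complete case analyses to assess robustness". No criterion is given for judging missing at random plausible, and no method is named for the case where it is judged implausible.

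The outcome for research question 1 is the number of weekly active school transports, from 0 to 10, built from children's daily self-reports (Research Question 1). The comparison is between cohorts of the same grade: "students in fifth grade at baseline (T_0_) will be compared with students in fifth grade from the same school at follow-up (T_1_) 1 year later".

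Two statements bear on how much data may be missing and why. Under SICTA: Previous Research, the pilot is said to have shown a need for recruitment that reaches children whatever their way of travelling to school. Under Expected Contributions, the pilot's "significant participant attrition due to study design constraints further underscored the need for a more adaptable approach". No rate of attrition or missing data is given for the pilot, and none is expected or assumed for this study.

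**The concern.** Two features of the rule do not do what they are meant to do.

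- **The condition.** Whether missing at random holds depends on values nobody observed. The extent and pattern of the gaps cannot settle it, so the choice of method rests on a judgement that the data cannot check.
- **The robustness check.** Complete-case analysis is assigned the purpose of assessing robustness. It does not relax missing at random; it generally needs stronger assumptions than imputation does. If non-response depends on the child's own travel, both analyses learn only from the reporters and go wrong in the same direction.

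The mechanism is plausible here because travel mode is the outcome, and the pilot's own lesson was that participation needs to be widened across travel modes. The follow-up report also comes two weeks after a campaign that rewards assignments and counts kilometres walked and cycled. A child who was driven to school may be less inclined to report then than a year earlier. That last step is inference, not something the protocol states. If it is right, the study could report a gain that partly reflects who answered, supported by a check that could not have shown otherwise.

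**Working it through.** The protocol gives no figure to reproduce: no sample size, standard deviation, effect size or missing-data rate. All numerical inputs below are assumptions.

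**1. Size of the overstatement**

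Let f be the fraction of a wave's participants without outcome data, and d the number of weekly trips by which non-reporters fall below comparable reporters.

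- True wave mean = reporter mean − f × d, so an analysis that treats non-reporters like comparable reporters overstates the wave mean by f × d.
- Overstatement of the gain, with the same d in both waves = f1 × d − f0 × d = d × (f1 − f0).
- Overstatement if only follow-up non-response is informative = d × f1.

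Assume f0 = 0.10 and f1 = 0.25:

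| d (trips/week) | Same d in both waves: d × 0.15 | Follow-up only: d × 0.25 |
|---|---|---|
| 1 | 0.15 | 0.25 |
| 2 | 0.30 | 0.50 |
| 3 | 0.45 | 0.75 |

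If f1 = f0 and d is the same in both waves, the bias in the gain is zero. If f1 is below f0, the gain is understated.

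**2. Can complete-case analysis reveal the problem?**

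This was simulated with a true effect of 0, two cohorts of 600, outcome mean 6, residual SD 2.5 and one covariate used in both the analysis and the imputation model. There were 10 imputations and 200 replicates per setting. Baseline non-response was unrelated to the outcome. At follow-up, the log-odds of non-response rose by 0, 0.5 or 1 for each 2.7 trips below the mean, which multiplies the odds by 1, about 1.65 or about 2.72. The entries are estimated effects in trips per week, so any departure from 0 is bias.

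| Underlying non-response | Dependence on outcome | Complete case | Multiple imputation |
|---|---|---|---|
| 10% | 0.5 | 0.147 | 0.146 |
| 10% | 1 | 0.289 | 0.289 |
| 20% | 0.5 | 0.233 | 0.234 |
| 20% | 1 | 0.455 | 0.453 |
| 30% | 0.5 | 0.330 | 0.333 |
| 30% | 1 | 0.659 | 0.657 |
| 40% | 0.5 | 0.443 | 0.442 |
| 40% | 1 | 0.815 | 0.817 |

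Without dependence, both were close to 0 (range −0.009 to 0.027). Monte Carlo error at 20% non-response is about 2.5 × √(2/480) / √200 = 0.01.

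The two methods never differ by more than 0.003 in the table, while the bias runs from about 0.15 to 0.82. Agreement between them therefore says nothing about informative non-response. An imputation model richer than the analysis model could separate them, but only as far as the added variables explain non-response. What remains would still go unexamined.

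**3. What a shifted imputation shows**

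Lowering imputed follow-up values by δ lowers the estimated gain by about f1 × δ. With f1 = 0.25, shifts of 1, 2 and 3 trips lower it by 0.25, 0.50 and 0.75. The point estimate reaches zero at about δ = gain / f1; a gain of 0.50 would vanish at δ = 0.50 / 0.25 = 2. The readers can judge whether that δ is credible.

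**The case against.** The strongest reply is that this is a condensed article. Its sentence, "Sensitivity analyses will include complete case analyses to assess robustness", does not claim to be a complete list, and further sensitivity analyses may stand in an analysis plan that is not shown. Making imputation conditional on missing at random is also common practice. The pilot's attrition is attributed to design constraints, and low willingness is reported for control-school children, an arm this design drops. Classroom reporting, daily text messages and paper forms should limit non-response. The magnitudes rest on assumed rates.

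Much of this stands. A reader might infer three stronger points that the text does not support:

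- **That robustness is checked by complete cases only.** The wording leaves room for more; complete case is merely the one check named.
- **That complete case is the fallback if missing at random is rejected, and the weaker method.** No fallback is named, and in the simulation complete case was no worse than imputation under informative non-response.
- **That sixth graders who left, or fourth graders who had not yet entered, count as missing.** No section says so. In the same-grade comparison each of these children has the one intended measurement. The difficulty arises only from the planned "analysis of covariance, with T_1_ as the dependent variable and T_0_ included as a covariate", which does not match the age-cohort design. That is a separate issue.

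The reply does not answer the central point. The article gives complete-case analysis a purpose that it cannot serve for the assumption that matters, and this is stated text rather than an omission.

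**Conclusion.** The concern holds in a limited form. The method is chosen by a judgement that observed data cannot settle, and the one named robustness check shares the bias it would need to expose. The illustrative overstatement is 0.15 to 0.45 trips per week if non-reporters fall short by 1 to 3 trips in both waves, and 0.25 to 0.75 if only follow-up non-response is informative. Both ranges assume 10% missing at baseline and 25% at follow-up. The direction assumes that non-active travellers are over-represented among non-reporters and that the problem is larger at follow-up. The protocol neither supports nor excludes these rates. The near-equality of the two methods rests on simulation with the same covariate in both models. It does not follow that the trial's result will be biased, only that the named check could not tell.

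**What to change.** Replace the conditional rule with a fixed one, before the follow-up data are analysed:

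- Define missing as a child who took part in a wave but lacks that wave's outcome.
- Use multiple imputation for these children without making it depend on the missing-at-random judgement. Include school, grade, wave, distance, gender and available BRACS and CIM answers in the imputation model. This alone does not remove bias from informative non-response, so the next step is needed.
- Add a delta-adjusted sensitivity analysis that lowers imputed follow-up transports by 1, 2 and 3 trips per week. State how values that would fall below 0 are handled, and report the delta at which the conclusion changes.
- Keep complete-case analysis as secondary, and do not describe its agreement with imputation as robustness to informative non-response.
- Report the fraction missing in each wave, since the bias depends on f0 and f1.

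The cost is a few sentences in the plan and a small amount of extra analysis. The Results section says follow-up collection is ongoing, so the change can still precede analysis. The drawback is a possibly less favourable statement on robustness.
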